### Sample size estimate

A sample size requirement of 36 was estimated to detect an effect size of 0.8, powered at 80% and alpha of 5% was chosen for a clinically meaningful estimate. The estimation was performed two-sided. Based on a paper by Melzer et al. [53] the investigators found that step execution (average foot-contact times) during the execution of cognitive tasks were 1414 ms ± 417 for elderly fallers and 1165 ± 352 in elderly non-fallers. It was estimated that 32 subjects are required to detect a clinical change in this parameter. For the current study we have used an attrition rate of 10% (32 × 1.10 = 36).

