**Methods/Design:**

The proposed water-based training program involves use of unpredictable, multi-directional perturbations in a group setting to evoke compensatory and volitional stepping responses. Perturbations are made by pushing slightly the subjects and by water turbulence, in 24 training sessions conducted over 12 weeks. Concurrent cognitive tasks during movement tasks are included. Principles of physical training and exercise including awareness, continuity, motivation, overload, periodicity, progression and specificity were used in the development of this novel program. Specific goals are to increase the speed of stepping responses and improve the postural control mechanism and physical functioning. A prospective, randomized, cross-over trial with concealed allocation, assessor blinding and intention-to-treat analysis will be performed to evaluate the efficacy of the water-based training program. A total of 36 community-dwelling adults (age 65–88) with no recent history of instability or falling will be assigned to either the perturbation-based training or a control group (no training). Voluntary step reaction times and postural stability using stabiliogram diffusion analysis will be tested before and after the 12 weeks of training.

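### The sample size of 32 (36 with attrition) does not follow from the stated effect of 0.8 at 80% power, and the cited data give an effect of about 0.65, so the stated power is unsupported

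*Protocol article*

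**What the plan says.** The Sample size estimate section of the protocol article gives the target as "A sample size requirement of 36 was estimated to detect an effect size of 0.8, powered at 80% and alpha of 5"%, and adds "The estimation was performed two-sided". It then cites dual-task foot-contact times of "1414 ms ± 417 for elderly fallers and 1165 ± 352 in elderly non-fallers" from an earlier study, and concludes: "It was estimated that 32 subjects are required to detect a clinical change in this parameter". Ten per cent attrition takes 32 to 36.

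The abstract makes 36 the total and describes the participants as adults "with no recent history of instability or falling". The Randomized Cross-Over Clinical Trial section specifies two groups that switch after a 1-month washout. The Statistical analysis section plans a repeated-measures analysis of variance, with order of intervention as a covariate.

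The sample size paragraph does not say which test was used, whether 0.8 is scaled by the between-person SD or by the SD of within-person differences, or what correlation was assumed.

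**The concern.** The paragraph prints an effect size, power, alpha, sidedness, source data and a number of subjects, and these do not fit together. The stated inputs do not lead to 32. The source data do not lead to 0.8. The source data also contrast fallers with non-fallers, which is not the change that training is expected to produce.

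The article may leave details to a fuller document, but the figures that it does print should agree. If they stand, the eventual result, and a null result above all, will be read against an 80% power claim that cannot be traced to any stated calculation.

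**Working it through.** **Inputs.** Effect 0.8, power 80%, two-sided alpha 5%, 32 subjects before attrition; fallers 1414 ms (SD 417), non-fallers 1165 ms (SD 352). All are from the Sample size estimate section. Correlations, and equal allocation of 16 completers per arm, are assumptions; the article gives neither.

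**Attrition step.** 32 × 1.10 = 35.2, rounded up to 36. Dividing instead, 32 / 0.9 = 35.6, also gives 36. This step is sound.

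**Does 0.8 at 80% power give 32?** With (1.960 + 0.842)² = 7.849:

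| Design | Normal approximation | t-based |
|---|---|---|
| Two groups | 2 × 7.849 / 0.64 = 24.5, so 25 per arm (50 total) | 26 per arm (52 total) |
| Paired, 0.8 on the difference scale | 7.849 / 0.64 = 12.3, so 13 | 15 |
| Cross-over, 0.8 on the between-person scale, correlation 0 | 2 × 7.849 / 0.64 = 24.5, so 25 | 27 |

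For the cross-over the SD of the difference is SD × √(2(1 − ρ)), so any positive correlation ρ lowers 27 further (20 at 0.3, 15 at 0.5). None of these is 32.

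**What effect do the cited data give?** Difference: 1414 − 1165 = 249 ms. SD pooled with equal weights (group sizes are not given): √((417² + 352²) / 2) = 385.9 ms. Effect: 249 / 385.9 = 0.645. Using one SD alone gives 249 / 417 = 0.60 or 249 / 352 = 0.71. No choice reaches 0.8. At 0.645 the t-based requirement is 39 per arm (78 total) for two groups, 21 if 0.645 is taken on the paired difference scale, and 40 in total for a cross-over at correlation 0.

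**Can 32 be recovered at all?** Yes, with the non-faller SD and the normal approximation: 2 × 7.849 / 0.707² = 31.4, so 32. The same number is a per-arm figure for a parallel design and a total for a cross-over at zero correlation. The effect is then 0.71, not 0.8. At 0.8, 32 in total also follows from a baseline-adjusted two-group comparison with a correlation of about 0.61, since 51 × (1 − 0.61²) is about 32. No correlation is stated.

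**Power with 32 completers** (two-sided 5%, t-based):

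| Analysis | Assumed correlation | Effect 0.8 | Effect 0.645 |
|---|---|---|---|
| Cross-over, no carryover | 0 | 87% | 71% |
| Cross-over, no carryover | 0.2 | 93% | 80% |
| Cross-over, no carryover | 0.5 | 99% | 94% |
| 3-month comparison, 16 per arm, unadjusted | none needed | 59% | 42% |
| 3-month comparison, baseline-adjusted | 0.5 | 71% | 53% |
| 3-month comparison, baseline-adjusted | 0.7 | 86% | 70% |

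The baseline-adjusted rows use effect / √(1 − ρ²) with 29 degrees of freedom.

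**The case against.** The strongest reply is that the trial is a cross-over and should be judged as one. With 32 completers it exceeds 80% power at 0.8 for any correlation of zero or more, and reaches about 80% at 0.645 once the correlation is near 0.2. This stands, provided there is no carryover. A reader might infer from the unadjusted two-group figures that the trial is underpowered. The documents do not support that: the Statistical analysis section does not name the 3-month comparison as primary, and even there baseline adjustment reaches about 80% at effect 0.8 with a correlation near 0.62.

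A reader might also infer that a per-arm figure was mistaken for a total. This is not shown, because 249 / 352 gives 32 equally well as a total for a zero-correlation cross-over.

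Next, the paragraph never says that 0.8 was derived from the cited means. The value may have been a separate choice, and on the within-person scale 0.8 can be a smaller change: with SD 386 and correlation 0.7 it is 0.8 × 386 × √0.6 = 239 ms, below the 249 ms gap. This is fair, but the scale is not stated, and the paragraph offers the cited data as the basis for 32.

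Finally, a faller/non-faller gap can serve as a yardstick of relevance. That is also fair. A reader might go further and say that participants should start at the non-faller mean of 1165 ms, leaving little room to improve. The documents do not establish this: the earlier study's definition of a faller is not given, and the exclusions under Recruitment of subjects do not mention falls. What remains is that the gap is not itself a training effect, and the paragraph does not say why it should be the target.

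**Conclusion.** The point holds as an inconsistency among printed figures. At 0.8, 80% power and two-sided 5%, the plain formulas give 52, 15, or at most 27 in total, not 32. The cited data give about 0.65 (0.60 to 0.71), not 0.8. The value 32 appears only under choices that the article does not state, and from the cited data only with an effect of 0.71.

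The 80% power claim is therefore unsupported, which is weaker than saying that power is inadequate. Depending on the analysis, effect and correlation, 32 completers give anything from 42% to 99%. The 0.65 assumes equal weighting of the two SDs, every correlation is an assumption, and the cross-over figures assume no carryover.

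**What to change.** Keep 36 participants and rewrite the paragraph so that its figures agree:

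- State the target effect and its scale (between-person SD or SD of within-person differences), the design formula and the assumed correlation.
- Either use the cited data as they stand (249 / 386 = 0.65) or justify a separate target in milliseconds for a training effect, and explain how 0.8 relates to it.
- Replace the 80% claim with the power that 32 completers give, marking correlations as assumptions. Report the planned cross-over analysis without carryover: at least 87% at 0.8, and about 71%, 80% and 94% at 0.65 for correlations 0, 0.2 and 0.5.
- Beside it, report the 3-month comparison, which carryover cannot affect: 59% and 42% unadjusted, and about 71–86% and 53–70% with baseline adjustment at correlations 0.5–0.7, for effects of 0.8 and 0.65 respectively.

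The cost is one paragraph and no extra participants. The stated power may become less favourable.

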## Discussion

This study is the first to use water-based training that includes perturbation exercises and water turbulence in a group setting as an intervention to reverse age-related impairments in the ability to step quickly and recover from loss of balance. It differs from previous studies done in the water in this area in a number of significant ways. To date, no study has proposed using a water-based training program that includes perturbations to train stepping reactions and investigate the potential of water turbulence to improve stability. Only four exercise regimens have proposed the use of perturbations to improve stepping in elderly persons; all were land-based exercises regimens [49-51,89].

The water-based training program that includes perturbation exercises as outlined is targeted specifically to: 1) step execution-recovery reactions that are known to be impaired in older adults and associated with increased falling risk [53]; 2) the water-turbulence during voluntary exercises challenges balance control in multiple directions; 3) the perturbations are applied by instructors and classmates in predictable and unpredictable manners that allow subjects to exercise safely and progress when needed. Based on our previous findings [53,66], ongoing cognitive exercises are included to increase the load and specificity of training.

We hypothesize that the novel water-based balance training that includes perturbation exercises will improve balance control and increase speed of stepping, and this should help to reduce the incidence of falls. Due to the limitation of randomized controlled cross-over trials, the investigation of effects on falling is beyond the abilities of the present study. The results of the present study will add evidence regarding the effectiveness of perturbation-based balance training programs, and will be novel in conducting the perturbation exercises in water against water resistance and in a group setting that provides cost-effective exercise programs for long-term improvement followed by maintenance of the training benefits.
